### Blinding

The present pilot study is designed as a double-blind trial, ensuring that neither the researchers conducting the study nor the participants will know which group they have been assigned to. To maintain the double-blind nature, the packages containing melatonin and placebo tablets will be coded as ‘A’ and ‘B’ at the start of the study by an individual not involved in the research process. This coding serves to blind the researchers. Furthermore, the supplement and placebo pills will be made identical in color, shape, smell, and appearance to blind the participants.

Labels on the supplement packs will stay hidden until the study is finished. However, if any adverse events occur, unblinding is allowed according to the Medical Ethics Committee’s guidelines to determine whether the patient received melatonin or a placebo. If dropout rates reach 15% or higher due to adverse effects, we will conduct an intention-to-treat (ITT) analysis.

### Intervention

Forty-six eligible women will be randomly assigned to either the melatonin group or the placebo group, with 23 participants in each group. Participants will take a 5 mg tablet one hour before bedtime with sufficient water and will be followed up for 8 weeks. The Tehran Darou Pharma & Food Supplement Company will supply the melatonin and placebo tablets, which will be identical in weight, size, shape, taste, color, odor, and packaging. Patients will receive the tablets during monthly study visits, with a total of three visits scheduled for the trial (before the intervention, after 1 month of intervention, and at the end of the intervention). Patients will be instructed on how to use their tablets and will receive weekly follow-up calls to improve response rates and fewer dropouts.

To enhance participant retention, the potential health benefits of melatonin will be explained, and the principal investigator will keep in regular contact with participants via phone calls.

Compliance will be assessed based on the number of unused tablets returned by each participant at the end of week four and the end of the trial. The remaining tablets will be counted to determine the total intake of the tablets. The total intake of tablets for each subject is calculated by subtracting the number of tablets unused from the number of tablets dispensed.

Participants can choose to leave the study at any point. Furthermore, the investigator has the authority to remove subjects from the study if they do not adhere to the protocol. Additionally, patients will be monitored for any adverse events following melatonin consumption. If any adverse events are attributed to melatonin, participants will be advised to discontinue the supplements and will be promptly referred to a specialist for further treatment.

It is important to note that no specific physical activity program, dietary recommendations, or regimens will be provided to the study subjects. Additionally, after considering the eligibility criteria, if subjects are being treated for any kind of disease during the study, they will not be deprived of routine treatment. Participants will receive either melatonin supplements or a placebo alongside their standard treatments.

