### Harms

According to the findings of the meta-analysis conducted by Menczel Schrire et al. [31], even daily consumption of doses ≥ 10 mg of melatonin supplements did not have any significant complications except drowsiness, headache, and dizziness. If any complications arise with the melatonin supplementation, the intervention will be halted immediately, and appropriate medical actions will be taken.

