### Data management and monitoring

An appointed monitor for the clinical trial will periodically oversee the study’s progression to protect the rights and welfare of the participants. This monitor will ensure compliance with the study protocol, ethical norms, and legal standards, verify the presence of necessary documents, and confirm the accurate recording of data. A member of the research team will be responsible for verifying the data’s coding, security, and storage procedures, as well as double-checking data entries and their corresponding values. Furthermore, participants will be followed for any negative reactions to melatonin intake. If such reactions are linked to melatonin use, affected individuals will be instructed to stop taking the supplement and immediately consult a specialist for additional care. In these instances, unblinding is allowed according to the criteria set by the Medical Ethics Committee.

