### Statistical analysis

Data will be analyzed statistically using SPSS 26.0 software, considering P values below 0.05 as indicative of statistical significance. The normality of data distribution will be checked using the Kolmogorov-Smirnov test, and an appropriate method will be applied to normalize variables that do not follow a normal distribution. Mean (standard deviation) and frequency (percentage) will be used to represent quantitative and qualitative variables, respectively. Independent sample t-tests will be used to evaluate differences in baseline means, while paired-sample t-tests will compare within-group differences. For variables assessed three times during the study (at the start, in the fourth week, and in the eighth week), a repeated measures ANOVA will be utilized. Additionally, Analysis of Covariance (ANCOVA) will assess the effects of the intervention between groups, adjusting for confounders such as baseline data and physical activity. In cases where dropout rates of 15% or more, an intention-to-treat (ITT) analysis will be performed. Missing data will be handled using multiple imputation methods.

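### The investigator may remove randomised women from the study for non-adherence, which leaves those removed before week 8 with no post-baseline value on any primary outcome

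*Protocol article*

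**What the plan says.** All references are to the protocol article.

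- **Removal.** Under Intervention, "the investigator has the authority to remove subjects from the study if they do not adhere to the protocol". The same section counts returned tablets at the end of week 4 and at the end of the trial.
- **Adverse events.** When an event is attributed to melatonin, "participants will be advised to discontinue the supplements and will be promptly referred to a specialist for further treatment" (Intervention). Under Harms, "If any complications arise with the melatonin supplementation, the intervention will be halted immediately". These sentences concern the tablets, whereas the removal sentence concerns the study.
- **Monitoring.** "patients will be monitored for any adverse events following melatonin consumption" (Intervention), and "participants will be followed for any negative reactions to melatonin intake" (Data management and monitoring).
- **Outcome timing.** The Abstract and Study outcomes place PFS, 2-AG and ghrelin at baseline and at the end only. Diet and body weight are also taken at week 4.
- **Analysis.** Under Blinding, "If dropout rates reach 15% or higher due to adverse effects, we will conduct an intention-to-treat (ITT) analysis". Under Statistical analysis, "In cases where dropout rates of 15% or more, an intention-to-treat (ITT) analysis will be performed", with multiple imputation for missing data.

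**The concern.** The clause is a discretionary exclusion after randomisation that ends data collection. That differs from choosing an analysis set: an analysis set can be redefined later, but a PFS score or blood sample that was never taken cannot be recovered.

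Whether a woman keeps taking tablets may depend on her arm and on how she is responding. Harms reports from a cited meta-analysis that melatonin "did not have any significant complications except drowsiness, headache, and dizziness". A woman who skips tablets on her own because of such effects would look non-adherent at the week 4 count and could be removed. If this happened more in one arm, or more among women with a particular response, the women measured at week 8 would no longer be the groups that were randomised.

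The pilot's stated main aim is to supply data for sizing a larger trial (Sample size). Estimates of effect, spread and attrition would then partly reflect investigator decisions.

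**Working it through.** **1. The plan's own figure.** Sample size raises 40 to 46 for 15% attrition: 40 × 1.15 = 46, or 23 per arm. Dividing instead gives 40 / 0.85 = 47.06, or 48 for equal arms; that small difference does not affect this point. The plan therefore allows for 46 − 40 = 6 losses. It gives no effect size, SD or power, so there is no power figure to reproduce.

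**2. What a removed woman leaves behind.** At the week 4 count she has baseline values on everything, and week 4 weight and diet. Her next primary measurement would be at week 8. If she is removed in between, PFS, 2-AG and ghrelin have no post-baseline value. Multiple imputation could use her baseline and perhaps her week 4 weight and diet. If women who leave the tablets also leave the study, there are no week 8 primary values from women off tablets to inform it. If removal depends on the unmeasured outcome, standard imputation does not correct for that.

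**3. The intention-to-treat trigger**, with dropout taken over all 46 women (the plan does not state the denominator):

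| Losses | Share of 46 | Share of 23 if all in one arm | 15% of 46 reached? |
|---|---|---|---|
| 6 | 13.0% | 26.1% | no |
| 7 | 15.2% | 30.4% | yes |

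If the rate were taken per arm, 3 of 23 (13.0%) would stay below the trigger and 4 of 23 (17.4%) would reach it. The Blinding wording counts only dropout due to adverse effects, so removals for non-adherence might not count at all under that version.

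**4. Possible shift in an arm mean.** If k of 23 women are removed and their mean differs by g SD from the other 23 − k, the observed mean differs from the full-arm mean by k × g / 23. Both k and g are assumed.

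| k | g = 0.25 | g = 0.5 | g = 1.0 |
|---|---|---|---|
| 3 | 0.03 SD | 0.07 SD | 0.13 SD |
| 6 | 0.07 SD | 0.13 SD | 0.26 SD |

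**5. Comparison with precision.** The difference detectable with 80% power at two-sided 0.05 (sidedness and power assumed; normal approximation) is (1.960 + 0.842) × √(1/n₁ + 1/n₂). This gives 0.83 SD at 23 v 23, 0.89 SD at 20 v 20 and 0.90 SD at 17 v 23. Lost precision is modest, so the main risk is selective loss.

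**The case against.** The strongest reply is that the adverse-event pathway is handled elsewhere. A reader might infer that a woman who stops tablets because of drowsiness or headache loses her safety follow-up, and that the removal clause contradicts the safety rule beside it. The text does not support this. A woman who stops on the advice given under Intervention and Harms is following the protocol, so the non-adherence clause does not reach her. Both monitoring sentences are general and are not limited to women still taking tablets. What remains are women who stop unprompted, or whose symptoms are not attributed to melatonin.

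Three other extensions also fail:

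- A woman flagged by the week 4 count is already at that visit, so the tablet count cannot cost the week 4 assessment.
- Sample size names no tolerability rate as an aim of the pilot.
- The lack of an adherence threshold in a condensed article is not a fault, because the full protocol may give one.

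It can also be said that blinded researchers have little scope to remove women selectively by arm, and that the shift rests on assumed inputs. Both points have weight. Blinding limits deliberate selection, but it does not prevent removals that follow from side effects, and unblinding is permitted after adverse events. The shift is a plausible range, not a prediction, and even its upper value is well below the detectable difference of 0.83 SD.

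None of this touches the core. The article states a rule of removal from the study, and a separate analysis plan could not recover data which that rule stops from being collected.

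**Conclusion.** The point holds as a weakness in trial conduct. A stated, discretionary post-randomisation exclusion can leave a woman with no post-baseline value on all three primary outcomes, and the planned analysis cannot repair that. Up to 6 of 46 losses (13.0%) would not trigger the intention-to-treat analysis when the rate is taken over both arms.

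The illustrated shift is 0.07 to 0.13 SD for 3 removals in an arm and 0.13 to 0.26 SD for 6. It assumes a 0.5 to 1 SD difference between removed and retained women; at 0.25 SD the figures are 0.03 and 0.07 SD. The 6-removal case puts the whole planned allowance in one arm and is the extreme. The documents give no expected number of removals and no evidence of imbalance between arms.

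The article does not show that safety follow-up ends for women who stop tablets, and that is not claimed here. The change is worth making because it is cheap and removes an avoidable route to selection bias.

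**What to change.** Replace the removal sentence under Intervention with one stating that:

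- non-adherence, or stopping tablets for any reason, does not end study participation;
- the week 4 and week 8 assessments, and the adverse-event monitoring already promised under Intervention and under Data management and monitoring, continue for all randomised women unless they withdraw consent;
- the reason for stopping tablets is recorded separately from the reason for leaving the study.

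This changes one clause and adds one recorded item. The visits and assays are already planned for 46 women. The downside is a few more week 8 assessments in women off tablets and some dilution of the estimated effect, because women no longer on tablets stay in the comparison. When tablets should be stopped is a clinical matter and is not judged here.

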### Harms

According to the findings of the meta-analysis conducted by Menczel Schrire et al. [31], even daily consumption of doses ≥ 10 mg of melatonin supplements did not have any significant complications except drowsiness, headache, and dizziness. If any complications arise with the melatonin supplementation, the intervention will be halted immediately, and appropriate medical actions will be taken.

### Study outcomes

The primary outcomes of the current trial are to reduce plasma levels of 2-AG, ghrelin, and the scores associated with hedonic eating. The secondary outcomes focus on dietary intake and body weight. Additionally, at the study’s outset, participants will provide their medical history and demographic information, including age, gender, educational background, and marital status.

The intensity of hedonic eating in the first phase of the project and at the end of the study will be measured using the PFS questionnaire, which has been previously validated for the Iranian population [28]. The questionnaire comprises 15 items across three subscales: the “Food Available (FA)” subscale evaluates public thoughts about foods, the “Food Present (FP)” subscale assesses attraction to directly available food, and the “Food Tasted (FT)” subscale evaluates attraction to foods that have a favorable/ preferred taste. The likert scale will be used for scoring, ranging from 1 to 5, where a higher score indicates greater hedonic hunger [32].

Plasma levels of 2-arachidonoylglycerol and acylated ghrelin will be measured before and after the study. For biochemical analysis, A 5 cc blood sample will be collected from each participant after a 10–12 hour fast for biochemical analyses. The blood will be placed in EDTA-coated tubes, centrifuged at 3000 rpm at 4 °C for 10 minutes, and then it will be stored at -80 °C to determine the plasma levels of 2-AG and acylated ghrelin. ELISA kits provided by ZellBio GmbH, [name], Germany, will be used to assess the plasma concentrations of 2-AG and acylated ghrelin.

For the evaluation of dietary intake, including total energy and macronutrient intake, participants will complete three 24-hour dietary recalls. This will include one weekend day and two weekdays, using a validated tool for dietary assessment. These recalls will be conducted through in person or phone interviews at the beginning of the study, after four weeks, and upon the completion of the intervention The Nutritionist IV software will be utilized to process and analyze the dietary information.

Body weight measurements will be taken using a Seca scale, accurate to 0.1 kg, at three key points: at the beginning of the study, after four weeks, and at the end of trial. During these measurements, participants will be wearing in light clothing.

Moreover, as a means of controlling for confounding factors, the validated short form of the Persian version of the International Physical Activity Questionnaire (IPAQ) will be used for the evaluation of physical activity at both the study’s outset and its completion [33,34].

### Ethics approval and consent to participate

The study protocol is registered in the Iranian Registry of Clinical Trials (IRCT20080904001197N22) and adheres to the Declaration of Helsinki Guidelines. Approval has been obtained from the Ethics Committee of Tabriz University of Medical Sciences, Iran (IR.TBZMED.REC.1402.075) [S2 File]. Before conducting the trial, any alterations to the study protocol—such as changes in objectives, design, patient population, sample size, procedures, or administrative aspects—must receive confirmation from the relevant departments. This confirmation ensures that patient safety and potential benefits are considered. Written informed consent will be obtained from all participants. Withdrawal of consent is possible at any time without loss of benefit.

### Data management and monitoring

An appointed monitor for the clinical trial will periodically oversee the study’s progression to protect the rights and welfare of the participants. This monitor will ensure compliance with the study protocol, ethical norms, and legal standards, verify the presence of necessary documents, and confirm the accurate recording of data. A member of the research team will be responsible for verifying the data’s coding, security, and storage procedures, as well as double-checking data entries and their corresponding values. Furthermore, participants will be followed for any negative reactions to melatonin intake. If such reactions are linked to melatonin use, affected individuals will be instructed to stop taking the supplement and immediately consult a specialist for additional care. In these instances, unblinding is allowed according to the criteria set by the Medical Ethics Committee.

### Auditing

This study will be overseen by the Ethics Committee of Tabriz University of Medical Sciences. The Committee will ensure the study’s quality, validity, and adherence to ethical standards through at least two monitoring sessions. Additionally, a report will be submitted to the auditor every three months.

### Statistical analysis

Data will be analyzed statistically using SPSS 26.0 software, considering P values below 0.05 as indicative of statistical significance. The normality of data distribution will be checked using the Kolmogorov-Smirnov test, and an appropriate method will be applied to normalize variables that do not follow a normal distribution. Mean (standard deviation) and frequency (percentage) will be used to represent quantitative and qualitative variables, respectively. Independent sample t-tests will be used to evaluate differences in baseline means, while paired-sample t-tests will compare within-group differences. For variables assessed three times during the study (at the start, in the fourth week, and in the eighth week), a repeated measures ANOVA will be utilized. Additionally, Analysis of Covariance (ANCOVA) will assess the effects of the intervention between groups, adjusting for confounders such as baseline data and physical activity. In cases where dropout rates of 15% or more, an intention-to-treat (ITT) analysis will be performed. Missing data will be handled using multiple imputation methods.

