Melatonin is a hormone with antioxidant and anti-inflammatory properties. It also has a significant role in glycemic homeostasis, modulation of white adipose tissue activity, lipid metabolism, and mitochondrial activity. In addition, melatonin increases brown adipose tissue volume and activity [19]. A meta-analysis in 2021 showed that taking daily doses of melatonin of ≤ 8 mg leads to weight loss. Nevertheless, it has been noted that the mechanisms underlying weight loss with melatonin supplementation are intricate and not completely comprehended [18]. In addition to the mechanisms mentioned, according to the results of animal studies, it appears that melatonin may also impact body weight by reducing hedonic eating. Some animal studies have shown a decrease in the serum level of ghrelin in mammals after melatonin supplementation [20–22]. In zebrafish, melatonin supplementation decreased the expression of the ghrelin hormone gene, and the CB1 receptor gene expression, as well as food intake [7,23]. Furthermore, norepinephrine, which is essential for the production of melatonin at night, down-regulated levels of some endocannabinoids, within the pineal gland of rats [24]. As previously mentioned, endocannabinoids and ghrelin are involved in the hedonic eating process. Therefore, melatonin supplementation may probably reduce food intake and hedonic eating by decreasing the levels of endocannabinoids, the expression of the ghrelin hormone gene, the level of ghrelin, and the expression of the CB1 receptor gene. In conclusion, it appears that conducting a clinical trial to examine the impact of melatonin supplementation on hedonic eating intensity and related biochemical biomarkers in overweight or obese individuals may be beneficial.

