### Strengths and limitations

This pilot study’s strengths lie in its use of a randomized, double-blind, placebo-controlled design to investigate the effects of melatonin supplementation on hedonic hunger intensity and related biochemical biomarkers in women with overweight/obesity, which is a novel approach. However, the research does have some limitations. Firstly, only two biochemical markers related to hedonic eating will be measured in this study. Secondly, despite employing a validated questionnaire for hedonic eating assessment, misclassification bias cannot be entirely eliminated. Lastly, despite accounting for potential changes in dietary intake or physical activity during statistical analysis, the participants’ self-reported dietary intake and physical activity could still influence the results. We anticipate that this trial will provide a general idea of the effectiveness of melatonin intervention in managing hedonic eating.

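### Read together, the protocol's sections indicate that the efficacy ANCOVA will adjust for changes in diet and activity measured after randomisation, which can bias the estimated melatonin effect

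*Protocol article*

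**What the plan says.** Four parts of the protocol article bear on this.

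- **Statistical analysis.** The between-group effect is estimated by ANCOVA, "adjusting for confounders such as baseline data and physical activity". Physical activity is listed apart from baseline data, without a time point. Dietary intake is not named.
- **Study outcomes, on physical activity.** The activity questionnaire (IPAQ) is included "as a means of controlling for confounding factors", for "the evaluation of physical activity at both the study’s outset and its completion".
- **Study outcomes, on diet.** "The secondary outcomes focus on dietary intake and body weight". Intake is recorded "at the beginning of the study, after four weeks, and upon the completion of the intervention".
- **Strengths and limitations.** Self-reported diet and activity could still influence the results, "despite accounting for potential changes in dietary intake or physical activity during statistical analysis".

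The Discussion adds the causal expectation: "melatonin supplementation may probably reduce food intake and hedonic eating". Nothing in the article limits the adjustment to baseline values.

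**The concern.** A change over the 8 weeks is known only after randomisation and may be a result of treatment. Such a variable is not a confounder of the randomised comparison, because treatment assignment cannot depend on it. It is a possible mediator, or an outcome in its own right.

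Conditioning on it has two consequences. If treatment moves the covariate and the covariate moves the outcome, that part of the effect is taken out of the estimate. If covariate and outcome share an unmeasured cause and treatment moves the covariate, a difference can appear where there is none. Either way, the adjusted difference no longer answers whether melatonin changes the outcome.

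Dietary intake is the clearest case, since it is both a secondary outcome and something the protocol expects melatonin to lower. Body weight is the most exposed outcome, because intake is an obvious route to weight change. The trial's stated main aim is to supply data for sizing a larger trial, so a distorted effect estimate would carry forward into that calculation.

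**Working it through.** **1. What the sections imply together.** The Statistical analysis section alone does not settle the timing. The completion IPAQ measurement has confounder control as its stated purpose, which a baseline-only adjustment would not need. The limitations paragraph refers to changes in diet or activity, and a change requires a value after randomisation. The natural joint reading is adjustment for post-randomisation values of activity and, by the limitations paragraph, of diet.

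**2. The plan's own figures.** There is no power calculation to reproduce. The only design figure is 40 participants raised to 46: 40 × 1.15 = 46. It is used here only to take 20 completers per arm. The standard error of a difference in SD units is √(2/20) = 0.316, about 0.32. Baseline adjustment would reduce it: with a baseline-to-final correlation of 0.7 (assumed), 0.316 × √(1 − 0.49) = 0.23.

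**3. Effect removed by mediation.** Let *a* be the shift in intake caused by melatonin (SD) and *b* the movement of the outcome per SD of intake. The article gives neither; 0.3 to 0.5 is assumed for each. The amount removed is *a* × *b*:

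- low: 0.3 × 0.3 = 0.09 SD
- high: 0.5 × 0.5 = 0.25 SD

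As an illustration, take a true total effect of −0.50 SD and *b* = 0.4 (assumed). The adjusted effect is −0.50 − *a* × *b*, with *a* negative:

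| Shift in covariate | Adjusted effect | Share lost |
|---|---|---|
| 0 | −0.50 | 0% |
| −0.3 SD | −0.50 + 0.12 = −0.38 | 24% |
| −0.5 SD | −0.50 + 0.20 = −0.30 | 40% |
| −0.8 SD | −0.50 + 0.32 = −0.18 | 64% |

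Large-sample least squares on 400,000 simulated participants agreed with each row to two decimals, allowing for simulation error. ANCOVA on the baseline outcome alone returned −0.50 throughout.

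For the next trial, required size scales with the inverse square of the effect. Planning on 0.38 instead of 0.50 multiplies it by (0.50/0.38)² = 1.7; planning on 0.30 multiplies it by (0.50/0.30)² = 2.8.

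**4. False difference with no true effect.** Assume a stable unmeasured cause with loading *l* = 0.4 to 0.6 on the outcome and on intake at every visit, no other correlation between them, and melatonin shifting intake by *a* = 0.3 to 0.5 SD.

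- *Final intake plus baseline outcome in the model.* Within arm, all pairwise correlations are *l*², so the slope on intake is *l*²/(1 + *l*²) and the false difference is *a* × *l*²/(1 + *l*²). Low: 0.3 × 0.16/1.16 = 0.04 SD. High: 0.5 × 0.36/1.36 = 0.13 SD.
- *Change in intake, without baseline intake.* The stable cause cancels in the change, the slope is zero, and so is the false difference.
- *Change in intake with baseline intake also in the model.* This is equivalent to entering final and baseline intake. The slope is *l*²/(1 + 2*l*²), giving 0.3 × 0.16/1.32 = 0.04 SD to 0.5 × 0.36/1.72 = 0.10 SD.

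**The case against.** The strongest reply is that the only sentence specifying the model names neither diet nor a time point for activity. Diet enters through one subordinate clause in a limitations paragraph, which names neither the ANCOVA nor any outcome. Variables measured three times are also to be analysed by repeated measures ANOVA, so reporting diet change by arm could be what was meant. This stands in part: the adjustment for diet change is inferred from several sections. It does not remove the point. The limitations paragraph presents accounting for changes as a safeguard against their influence on the results, which describes adjustment better than it describes an outcome analysis. On either reading the sections need to be reconciled.

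Several stronger readings are tempting but not supported.

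- *That the adjustment will certainly bias the estimate.* Bias in the total effect requires melatonin to shift the covariate; with no shift there is none.
- *That activity carries the same problem as diet.* The article hypothesises no effect of melatonin on activity.
- *That the protocol makes intake the cause of hedonic eating.* It puts the two side by side as results of lower endocannabinoids and ghrelin, so the slope *b* for the hedonic eating score is purely an assumption.
- *That the false difference reaches 0.05 to 0.18 SD.* That is *a* × *l*² (0.3 × 0.16 to 0.5 × 0.36). It leaves out the baseline outcome, although the plan adjusts for baseline data.
- *That the open covariate list and the baseline t-tests show covariates will be picked from the data.* The article does not link the tests to covariate choice, and a full list is commonly left to the full protocol or analysis plan. Neither carries this point.

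**Conclusion.** The point holds as a risk that the plan's own wording creates. Read together, the sections indicate that the efficacy ANCOVA will use post-randomisation activity and, from the limitations paragraph, diet. For diet the risk is concrete, because the protocol expects melatonin to reduce intake and names intake as an outcome. For activity it is conditional on an effect that the protocol does not propose.

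Under the assumed inputs, 0.09 to 0.25 SD of a real effect would be lost. That is below the unadjusted standard error of 0.32 SD; the upper end is about equal to a baseline-adjusted one. The false difference under no effect is about 0.04 to 0.13 SD with final intake and the baseline outcome in the model, and zero for a change score without baseline intake if the shared cause is stable. All of these sizes rest on inputs that the article does not give. The distortion is modest beside the imprecision of a pilot, but it does not shrink with more participants and would be passed on to the larger trial's sample size.

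**What to change.** Restrict the efficacy ANCOVA to the baseline value of the outcome, the BMI stratum (the stratification factor) and, if wanted, baseline IPAQ and baseline intake. State that no variable measured after randomisation enters it. Report week-8 activity and diet by arm. Label any model that includes their changes as exploratory. Amend the Statistical analysis section, the physical activity paragraph under Study outcomes, and the sentence in Strengths and limitations so that all three agree.

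The cost is wording only: no new data, visits or participants. The change should be made before the groups are compared.
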